#### RE-AIM: Reach

To determine the representativeness of survivors of burn injuries, participant demographics will be compared with those of nonparticipants using the Dutch Burn Repository R3. Nonparticipants will include both survivors of burn injuries who did not meet the eligibility criteria and eligible survivors of burn injuries who declined participation. We will compare some characteristics, such as sex, age, total body surface area burned, operation, and length of stay. Comparisons will be descriptive in nature and will be used to assess the representativeness of the study sample and to explore potential selection effects, rather than to draw causal inferences.

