### Recruitment

As of July 15, 2022, all survivors of burn injuries receiving burn care in one of the 3 centers are asked by a nurse practitioner or aftercare nurse to complete the routinely collected value-based health care burns core set for adult survivors of burn injuries as part of the Dutch Burn Repository R3 and the BORN [58]. In addition to the routinely collected core set data, survivors of burn injuries who participate during the pre- and postimplementation phases of this study will be asked to complete additional questionnaires. A nurse practitioner or aftercare nurse will introduce the study to eligible patients and provide a patient information letter. After an appropriate consideration time (2 d), a member of the center’s research team will answer any questions about the study and take informed consent. By involving the nurse practitioners and aftercare nurses, all eligible survivors of burn injuries will be reached.

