##### RE-AIM: Effectiveness

###### Effectiveness on Health Outcomes of Survivors of Burn Injuries – Coprimary Outcome Measure

To examine if participants in the control and intervention groups are comparable on baseline demographics and clinical outcomes, chi-square tests will be used for categorical data, and Mann-Whitney or independent *t* tests will be used for numerical data. To test the effectiveness of BreeZe on health outcomes of survivors of burn injuries, we will conduct (multilevel) regression analyses for repeated measurements, with measurement occasions nested in patients. Variables that might explain differences between measurement occasions (eg, time since injury, time since discharge, season, and time since intervention started) or patient (eg, age and sex) will be tested. We expect that the variance between measurement occasions will be largely explained at the level of patients. To account for the difference between centers, we will add 2 dummy variables (with center 1 being the reference center) to these analyses [55].

In addition, as control and intervention participants are enrolled in different calendar periods in different centers due to the stepped-wedge design, we will test in the (multilevel) regression analyses whether time can best be modeled continuously (since discharge) or as a categorical variable. The latter is interpreted more easily and is more often used in clinical settings, but does increase the degrees of freedom in the model. We will also document major changes in burn care organization, staffing, or parallel initiatives during the study and consider these in sensitivity analyses and in the interpretation of our findings.

The primary data analyses will be conducted on the data of the PiH questionnaire. In the multilevel analyses, the patient’s PiH score at a certain moment is the dependent variable. In addition, we will use three different approaches to provide a comprehensive evaluation of the intervention’s impact. First, for each group, the number and percentage of participants who have improved by at least 8 points on their self-management skills will be calculated, and the difference between groups will be tested with a chi-square test. We consider an improvement of 8 points a clinically relevant score, based on a face validity assessment by burn care nurse practitioners.

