## Results

This research is part of a larger project, which was funded in January 2022. Participant recruitment ended on June 30, 2025. In total, 42 participants are included in the control group, and 53 participants are included in the intervention group. Follow-up data collection is currently ongoing and will end in July 2026. Data analysis will start in August 2026, and the results are expected to be published in May 2027.

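### The supplementary 8-point responder comparison uses an unadjusted chi-square although the centre mix of the two non-randomised groups differs by design

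*Protocol article*

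**What the plan says.** The main effectiveness analysis is a multilevel regression: "In the multilevel analyses, the patient’s PiH score at a certain moment is the dependent variable" (Statistical Methods, coprimary effectiveness outcome). Centre enters it without condition: "To account for the difference between centers, we will add 2 dummy variables (with center 1 being the reference center) to these analyses". Patient-level and occasion-level variables are given as examples and "or patient (eg, age and sex) will be tested". The same section acknowledges that the two groups are enrolled in different calendar periods and in different centres.

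It then continues: "In addition, we will use three different approaches to provide a comprehensive evaluation of the intervention’s impact". The first of the three is the share of participants in each group who improve by at least 8 PiH points, for which "the difference between groups will be tested with a chi-square test". No stratification or covariate is mentioned for this test.

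Sequence Generation says that the order of the centres follows perceived organisational readiness, not randomisation. The Results section reports that "In total, 42 participants are included in the control group, and 53 participants are included in the intervention group".

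**The concern.** A two-group chi-square treats the groups as exchangeable. Here they are not, and the protocol says so just before it specifies the test. Centre 1 contributes little control time and much intervention time, and centre 3 the reverse. Any difference in responder rate between those centres therefore passes straight into the group comparison.

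The result will matter when the trial is read. Eight points is the plan's clinically relevant difference and the basis of its sample size, so the responder percentages are likely to be quoted beside the regression estimate. If one analysis carries centre and the other does not, the two can differ through confounding alone, with no planned way to tell that apart from a real difference between mean change and responder share.

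**Working it through.** The protocol gives no power or sample size for the responder comparison, so there is no figure of its own to reproduce.

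**Inputs from the protocol.** Control recruitment starts in April 2024 in all centres (Trial Design). The switch is in June, September and November 2024 for centres 1, 2 and 3 (Trial Design). Recruitment ends on 30 June 2025, with 42 control and 53 intervention participants (Results).

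**Assumptions.** Equal recruitment per centre-month; switch at the start of the stated month; responder rates by centre as given below. The protocol reports neither counts nor responder rates by centre.

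**Step 1: centre mix.**
- Control centre-months: 2 + 5 + 7 = 14, so 14%, 36% and 50%.
- Intervention centre-months: 13 + 10 + 8 = 31, so 42%, 32% and 26%.
- With a mid-month switch: 16/35/48% against 42/32/25%, almost the same.

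**Step 2: false difference with no intervention effect,** for assumed responder rates of 45/37.5/30%.
- Control: (2 × 45 + 5 × 37.5 + 7 × 30)/14 = 34.8%.
- Intervention: (13 × 45 + 10 × 37.5 + 8 × 30)/31 = 38.7%.
- Difference: 3.9 points.

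**Step 3: type I error.**
- Pooled rate: (42 × 34.8 + 53 × 38.7)/95 = 37.0%.
- Standard error: √[0.370 × 0.630 × (1/42 + 1/53)] = 0.0997.
- Shift in standard errors: 0.0389/0.0997 = 0.39.
- P(|Z + 0.39| > 1.96) = 0.058 + 0.009, about 6.8% instead of 5%.

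**Step 4: other assumed gaps** (simulation at 42/53, 20,000 runs, no intervention effect).

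| Rates, centres 1/2/3 | False difference | Unadjusted | Centre-stratified |
|---|---|---|---|
| 40/40/40% | 0 | 5.2% | 4.9% |
| 50/40/30% | +5.2 points | 7.8% | 4.9% |
| 55/40/25% | +7.8 points | 11.4% | 4.8% |
| 60/40/20% | +10.4 points | 17.9% | 5.1% |

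Reversing the gradient (30/40/50%) gives −5.2 points, so the error can favour either group.

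**Step 5: price of adjusting for centre.** Expected counts are 6/15/21 control and 22.2/17.1/13.7 intervention.
- Effective information without centre: 42 × 53/95 = 23.4.
- With centre: 6 × 22.2/28.2 + 15 × 17.1/32.1 + 21 × 13.7/34.7 = 4.7 + 8.0 + 8.3 = 21.0.
- Variance ratio: 23.4/21.0 = 1.12.

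**Step 6: price of adding calendar period.** Weighted least squares was run on the 45 centre-month cells (3 centres × 15 months), with weights 42/14 = 3.0 per control cell and 53/31 = 1.71 per intervention cell. Relative to no adjustment, the variance of the group effect rises about 3.2-fold with a linear month term, 3.4-fold with quarters and 4.4-fold with months. The reason is the layout: all centres are in control before June 2024 and none after centre 3 switches in November, so only the months between separate group from calendar time.

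**Step 7: what centre adjustment does not do.** With equal centre rates of 40% and a 10-point calendar or case-mix shift between phases, the false-positive rate is 16.5% unadjusted and 15.2% centre-stratified.

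**The case against.** The strongest reply is that the chi-square is supplementary. The main analysis is the PiH regression, which has the centre dummies. A reader might infer that the main comparison also leaves centre mix uncontrolled; the text does not support that, and the point is confined to the responder test.

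The size is also open to challenge. The responder rates are assumed, Burn Centers describes the patient populations as generally comparable, and a bias of 3.9 points is small beside a standard error of about 10. That stands: with equal rates across centres the chi-square holds its level. But comparable populations do not guarantee equal responder rates, since the same section reports differences in how aftercare is organised. The imbalance in mix follows from the dates, subject to even recruitment.

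Two further inferences are tempting and should not be drawn.
- **That covariates stay in the model only if significant.** The plan says they will be tested. It gives no retention rule, and such a rule may properly sit in a document not shown.
- **That enrolment fell after the switch and so shows selection.** The clinical staff do introduce the study: "A nurse practitioner or aftercare nurse will introduce the study to eligible patients and provide a patient information letter". The rates are 42 over 14 to 17 control centre-months and 53 over 28 to 31 intervention centre-months, a ratio of 0.57 to 0.77. The exact p value runs from 0.008 to 0.20 with the assumed switch day. Recruitment is consecutive, a research-team member takes consent, and season alone could lower the rate. This is no evidence of selection.

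**Conclusion.** The point holds for the responder test alone. As specified, it is open to centre confounding that the design creates and the protocol itself recognises. The size cannot be known from the document: about 4 points and a type I error near 7% for an assumed 15-point gap between centres 1 and 3, up to about 10 points and 18% for a 40-point gap, and nothing if centres respond alike. These figures rest on equal recruitment per centre and a start-of-month switch; a mid-month switch barely changes the mix. Since adjusting for centre is cheap, the unadjusted test should not be the inferential one. Calendar trend is a separate exposure that centre adjustment does not remove and that this design can address only at a high price in precision.

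**What to change.** Before the analysis planned for August 2026:

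1. Analyse the 8-point responder outcome with a logistic or risk-difference model that contains group and the same two centre dummies as the main model. Keep the chi-square and raw percentages as descriptive.
2. Add a small fixed set of pre-treatment covariates: age, sex and burned surface area. All three are already collected from the burn registry for eligible patients (Data Collection Methods) and already named for the reach comparison: "such as sex, age, total body surface area burned, operation, and length of stay". Keep the same set in the PiH regression whatever its significance, so that the two analyses answer the same question.
3. Add calendar period as a sensitivity analysis, and state that without it a calendar trend between phases is not removed.

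The cost of items 1 and 2 is wording, a few degrees of freedom and about 12% more variance from centre. Item 3 raises the variance of the group effect about three- to fourfold, which is why it should not replace the centre-adjusted analysis. No new data are needed.

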### Participant Timeline

The participant timelines illustrated in Table 2 (for survivors of burn injuries) and Table 3 (for health care professionals) outline the different assessment time points of the study.

**Table 2. T2:** Timeline for participating survivors of burn injuries: enrollment, interventions, and assessments.

	Study period – survivors of burn injuries				
	Enrollment	Allocation	Postallocation		Closeout
	Before discharge	At discharge	T1 (2 weeks postdischarge)	T2 (6 months postdischarge)	T3 (12 months postdischarge)
Enrollment					
Eligibility screen	✓				
Informed consent	✓				
Allocation		✓			
Interventions					
Control (usual care)^a^			✓	✓	✓
BreeZe aftercare^a^			✓	✓	✓
Assessments					
Demographics		✓			
Self-management skills (PiH^b^) [34]			✓	✓	✓
Self-regulation (SeRA^c^) [35]			✓	✓	✓
Participation (MeEAP^d^) [36]			✓	✓	
Daily activities (EQ-5D-5L) [37]			✓	✓	✓
Self-care (EQ-5D-5L) [37]			✓	✓	✓
Dependency			✓	✓	✓
Return to work or school (ICHOM^e^) [38]				✓	✓
Patient centeredness (CAHPS^f^) [39,53]				✓	
Quality of life (EQ-5D-5L) [37]			✓	✓	✓

a Duration of usual or BreeZe aftercare depends on the personal trajectory of the survivor of burn injuries.

b PiH: Partners in Health scale.

c SeRA: Self-Regulation Assessment.

d MeEAP: Measure of Experiential Aspects of Participation.

e ICHOM: Adjusted International Consortium for Health Outcomes Measurement.

f CAHPS: Consumer Assessment of Health Plan Survey.

**Table 3. T3:** Timeline for participating health care professionals: enrollment, interventions, and assessments.

	Study period – health care professionals				
	Enrollment	Allocation	Postallocation		Closeout
	Preimplementation phase	Implementation phase	T1 (3 months postimplementation phase)	T2 (6 months post implementation phase)	T3 (12 months postimplementation phase)
Enrollment					
Eligibility screen	✓				
Informed consent	✓				
Allocation		✓			
Interventions					
Training		✓			
Assessments					
Demographics	✓				
Self-management support skills (SEPSS-36^a^) [40]	✓		✓	✓	✓
Need-supportive counseling (COUNSEL-CCE^b^ and NCIT^c^) [41,42]	✓		✓		✓
Maintenance (PRESS^d^) [44]				✓	✓
Maintenance (CSAT^e^ ) [45]			✓		✓
CFIR^f^-informed interviews				✓	

a SEPSS-36: Self-Efficacy and Performance in Self-Management Support Questionnaire.

b COUNSEL-CCE: Coding and Observing Need-Supportive Counselling in Chronic Care Encounters.

c NCIT: Nurse-Child Interaction Taxonomy.

d PRESS: Provider Report of Sustainment Scale.

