### Sample Size

To estimate sample size, we used a power calculation based on our primary outcome, which is self-management skills measured by the PiH questionnaire. As no minimum clinically important difference is established in the literature, 2 burn care nurse practitioners examined the PiH and considered an improvement of 8 points as clinically relevant. Based on this face-validity score and a previous dataset with PiH data from survivors of burn injuries collected with the Burn Centers Outcomes Registry the Netherlands (BORN), a mean difference of 8 points between the control and intervention group is feasible. As there is no validated stepped-wedge–specific sample size calculator for this outcome, we used a pragmatic approximation based on this predefined clinically relevant difference we established. In addition, as there is no data available on potential ICCs and we have a small number of burn centers, we will take center difference later on into account by adding 2 dummy variables (with center 1 being the reference center) in our analyses [55]. For the sample size calculation, we used the online sample size calculator of the University of British Columbia [56]. We aim to obtain 80% power with a 2-sided significance level of 0.05. Due to the stepped-wedge design of our study, our allocation rate for the control group:intervention group will be 0.625:1. With an adjustment of 20% for dropouts, missing data, and fixed time effects taken into account, we calculated that 57 participants in the control group and 89 participants in the intervention group will be sufficient. This amount (n=146) is deemed sufficient for (multilevel) regression analyses using the MIwiN statistical program, version 3.10 [57].

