Second, to examine whether greater improvement is achieved by individuals with low compared with high baseline scores, we will create 2 groups based on the median score. Besides a baseline effect and an intervention effect, an interaction effect will be tested.

Third, for each participant, we will tally the number of PiH questions where they score 6 or higher, as such a score will be considered clinically satisfactory. This sum score will range from 0 to 12 and will also be used as a dependent variable in a regression analysis with group and time as possible predictors. Our hypothesis is that there will be an increase in this sum score, which will be greater in the intervention group compared to the control group.

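### Testing whether low scorers gain more through a median split of baseline PiH wastes information; a continuous baseline-by-group interaction is a cheap improvement to this supplementary analysis

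*Protocol article*

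**What the plan says.** The main analysis, under the coprimary effectiveness outcome in Statistical Methods, is a repeated-measures multilevel regression in which the "PiH score at a certain moment is the dependent variable". PiH is therefore handled there as a numeric score. Table 1 gives its range as 0-96. Table 2 schedules it at 2 weeks, 6 months and 12 months after discharge, so baseline here is presumably the 2-week value.

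The section then adds supplementary analyses: "In addition, we will use three different approaches to provide a comprehensive evaluation of the intervention". The second of these asks whether people who start low improve more than people who start high. Its method is stated: "we will create 2 groups based on the median score". The test follows: "Besides a baseline effect and an intervention effect, an interaction effect will be tested". No interaction with the undivided baseline score is described.

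The Sample Size section covers only the main comparison ("We aim to obtain 80% power with a 2-sided significance level of 0.05", for 8 PiH points). It gives no SD, no baseline-follow-up correlation, and no effect size or power for the interaction.

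**The concern.** The question concerns a gradient: does the benefit of BreeZe change as the starting score rises? A cut at the sample median treats two patients one point apart as belonging to opposite classes, and two patients far apart in the same half as identical. The cut also moves with the sample, so the low and high groups found here cannot be carried over directly to another cohort. The article gives no clinical reason to expect a jump at the median.

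Interaction tests are weak in small studies. Recruitment closed at 42 + 53 = 95 against a planned 57 + 89 = 146, so the sample can no longer be enlarged to compensate. The efficiency of the analysis can still be improved. What is at stake is the evidence on which patients benefit most, not the overall effect of BreeZe.

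**Working it through.** **1. The plan's own figure.** There is no power figure for the interaction to reproduce. The main-comparison sample size gives a working SD. With a difference of 8 points, two-sided 0.05, 80% power and ratio 1.6 (= 1/0.625):

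n(control) = (1 + 1/1.6) × SD² × (1.960 + 0.842)² / 8².

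With SD = 15 this is 1.625 × 225 × 7.85 / 64 ≈ 44.8, so 45 control and 72 intervention. Dividing by 0.8 gives 57 and 90, against the stated 57 and 89. SD 15 is thus compatible with the plan, but it is inferred and not stated there.

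**2. Information kept by the split.** For a linear interaction, the share kept is the squared correlation between the score and its above/below-median indicator.
- Normal baseline: 2/π = 0.637, so 36.3% is lost (equivalent sample inflation 1/0.637 = 1.57).
- Uniform baseline: 0.75, so 25% is lost. Skewed baselines lose more than the normal case.

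**3. What that means for power in general.** Power after the split = Φ[(1.960 + z_power) × √(2/π) − 1.960], where z_power is the normal quantile of the power with the continuous score.

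| Continuous | Split | Loss (points) |
|---|---|---|
| 30% | 21% | 9 |
| 50% | 35% | 15 |
| 80% | 61% | 19 |
| 90% | 73% | 17 |
| 95% | 82% | 13 |

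**4. A worked scenario at the recruited size.** Assumptions: 42 and 53 patients, SD 15, correlation 0.6, normal baseline, one complete follow-up, low scorers gaining more. The residual SD is 15 × √(1 − 0.36) = 12.

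Continuous test: SE of the slope difference = (12/15) × √(1/42 + 1/53) = 0.165.

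Split test: a slope difference g appears as a difference of g × 15 × 2√(2/π) = 23.9g points between halves. The residual variance in each arm rises by (arm slope)² × 225 × (1 − 2/π), because baseline still varies within each half. For g = 0.3 the control variance is 144 + 0.36 × 81.8 = 173.4 and the intervention variance is 144 + 0.09 × 81.8 = 151.4. The SE is 2 × √(173.4/42 + 151.4/53) = 5.29, and z = 7.18/5.29 = 1.36.

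| g | Difference between halves (points) | Continuous: formula / simulated | Split: formula / simulated |
|---|---|---|---|
| 0.167 | 4.0 | 17% / 16% | 12% / 11% |
| 0.2 | 4.8 | 23% / 22% | 15% / 15% |
| 0.3 | 7.2 | 44% / 43% | 27% / 28% |
| 0.4 | 9.6 | 68% / 65% | 44% / 44% |
| 0.5 | 12.0 | 86% / 83% | 63% / 62% |

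The simulated losses are 15, 21 and 21 points for g = 0.3, 0.4 and 0.5. For g = 0.167 to 0.2, repeated runs gave about 4 to 8 points. At the planned 57 and 89, the losses for g = 0.3, 0.4 and 0.5 were 20, 22 and 16 points.

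**5. When the split wins.** With a true step exactly at the median, the split was the more powerful test (77% v 58% in one setting, 39% v 28% in another).

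**The case against.** The strongest reply is that the loss is large only for large interactions. Slope differences of 0.3 to 0.5 mean the effect differs between halves by about 7 to 12 points, when the whole main effect planned for is 8. For a 4-point difference, half the main effect, power is about 16% against 11%, and changing the analysis rescues little. At the recruited size, 80% power with the continuous score needs a slope difference of about 0.58 residual SDs per baseline SD. That is 0.58 × 12/15 = 0.46 per PiH point, or about 11 points between halves. This objection stands. The main limit is the 95 patients, and the power cost must be stated conditionally.

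It is also fair that the calculation is a single-follow-up linear regression with complete data, whereas the plan is a repeated-measures multilevel model with center dummies. The absolute powers above are therefore not this trial's. SD, correlation, normality and linearity are all assumed, and PiH is bounded at 0 and 96.

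A reader might infer that a real gradient would probably be reported as absent because of the split. The figures do not support that. At a slope difference of 0.5 the split still detects it about 62% of the time. At 0.3 the continuous test also misses it more often than not. Among the slopes tried, only near 0.4 does the choice of test move the likely result from one side of even odds to the other.

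Finally, sample quartiles depend on the sample just as a median does. A continuous model avoids this because the effect can be read off at any stated PiH value.

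None of this makes the split preferable, since the article gives no reason to expect a step at the median.

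**Conclusion.** The point holds as an efficiency improvement to a supplementary analysis. With a roughly normal baseline and linear modification, the median split keeps about 64% of the information for the interaction test (about 75% if uniform). Under SD 15, correlation 0.6, 42 v 53 and one follow-up, that is about 15 to 21 power points where the continuous test would have roughly 40-85% power, and about 4 to 8 points for smaller interactions, where neither test is strong.

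Two stronger readings should be resisted. One is a fixed power loss that applies whatever the true interaction; the article gives none of the quantities needed to support it. The other is that the coprimary result is compromised. The split belongs to one of three added analyses, and the main PiH model and its intervention estimate do not depend on it.

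**What to change.** In the second supplementary approach, replace the test on the two halves with an interaction between group and baseline PiH as a continuous, centered covariate, within the regression model already planned. Add one curvature term as a check on linearity. Report the intervention effect with its confidence interval at stated PiH values, for example the quartiles with their actual scores given. Keep the low/high table as description only.

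The cost is a line or two of analysis text and no new data. The downside is the assumption of a linear gradient, which the curvature term checks only in part. Analysis is due to start in August 2026, so the change can be written down before then.
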